## Procedures for reporting Adverse Events

### Solicited AEs

Participants will be asked to record local and systemic AE's for 7 days in their paper diary.

Participants are asked to fill in these AE's in a digital questionnaire 8 days after boost.

Local solicited AEs; pain, redness, warmth, swelling

Systemic solicited AEs; joint pain, fatigue, fever, chills, headache, muscle pain, nausea

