#### 6.4 Summary of known and potential risks and benefits

##### Potential risks from vaccine administration (Moderna / Pfizer).

Hypersensitivity to the active substance or to any of the excipients.

The most common side effects are usually mild or moderate and got better within a few days after vaccination. Local and systemic adverse reactions were reported more frequently after dose 2 than after dose 1.

Very common (>10%): pain and/or swelling at the injection site, lymphadenopathy (axillary on the same side as the injection site), headache, nausea, vomiting, muscle and joint pain, fatigue, chills, and fever.

Common (1-10%): (itchy) rash or redness at the injection side. Skin rash.

Uncommon (0.1-1%): itching at the injection side, insomnia, malaise, pain in extremities, tremor, sneezing, sore throat, hyperhidrosis, muscle weakness, backache, and asthenia.

Rare (0.01-0.1%): hypersensitivity (allergic reaction of skin and underlying tissue), urticaria. Acute peripheral facial paralysis or palsy (in reports seen from day 22 to day 32 after the 2nd dose with Moderna and from day 3 to 48 after vaccination with Pfizer).

Facial swelling reported in individuals who have had facial dermal fillers in the past (Moderna).

Very rare (<0.01%): thrombosis in combination with thrombocytopenia; includes venous thrombosis such as cerebral venous sinus thrombosis, splanchnic venous thrombosis and arterial thrombosis.

Furthermore, anaphylaxis and hypersensitivity have been reported.

As for all vaccines, the vaccines will be given under close supervision with appropriate medical treatment available.

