#### 8.1.2 Secondary study parameters/endpoints

##### Secondary endpoints:

In addition to the primary endpoints defined above, this study will address the following secondary objectives:

1. *What is the difference in booster immunogenicity comparing a direct boost with a postponed boost?*

**Outcome:** Level of antibodies and T-cell responses 7 and 28 days post boost in DB versus PPB group.

2. *What is the breadth of the immune responses after booster vaccination?*

**Outcome:** PRNT against relevant variants in a random selection of study participants.

3. *What is the predictive value of immune responses on day 7 post boost?*

**Outcome:** Relationship between antibodies and T-cell responses on day 7 and 28 post boost.

4. *What is the difference in reactogenicity 7 days after boost comparing the Janssen and mRNA primed HCW?*

**Outcome:** Adverse events (AE) first 7 days after an additional boost between Janssen and mRNA primed HCW.

5. *Initial examination of breakthrough infections before and during study period*

**Outcome:** Database of breakthrough infections in included participants based on positive PCR, self-reported positive lateral flow test, or detection of N-specific antibodies.

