**All participants DB group after 7 days (day 7)**

- Request to fill a side effects + COVID-19 questionnaire (solicited local & systemic reactions)
- One serum tube (8.5ml)
- One lithium heparin tube (10ml)
- Four lithium heparin tubes (4x10ml)\*

\*only in the detailed immunological assessment group

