### 9.2 AEs, SAEs and SUSARs

#### 9.2.1 Adverse events (Aes)

Adverse events are defined as any undesirable experience occurring to a subject during the study, whether or not considered related to the trial procedure. All adverse events reported spontaneously by the subject or observed by the investigator or his staff will be recorded. However, given the setting of a large outbreak, the registration of Aes is not feasible and will not serve the safety of the participants. Therefore, Aes will not be reported.

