### Unsolicited AEs

All local and systemic AEs occurring 28 days following boost observed by the Investigator or reported by the participant.

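### The solicited reaction list leaves out axillary lymphadenopathy and vomiting, the only two reactions the protocol calls very common that participants are not asked about

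*Protocol*

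**What the plan says.** Secondary objective 4 (protocol sections 2, 8.1.2 and 10.2) is reactogenicity after the boost. Its outcome is "Adverse events (AE) first 7 days after an additional boost between Janssen and mRNA primed HCW".

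The instrument is set out under Solicited AEs, within the procedures for reporting adverse events in section 9. Participants keep a 7-day paper diary and transfer it to a digital questionnaire on day 8. Two lists are fixed there:

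- "Local solicited AEs; pain, redness, warmth, swelling"
- "Systemic solicited AEs; joint pain, fatigue, fever, chills, headache, muscle pain, nausea"

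For the direct boost group, section 8.3 describes the day 7 form in the same terms: "Request to fill a side effects + COVID-19 questionnaire (solicited local & systemic reactions".

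Section 6.4, on the known risks of the Moderna and Pfizer vaccines, gives the top frequency class as "Very common (>10%): pain and/or swelling at the injection site, lymphadenopathy (axillary on the same side as the injection site), headache, nausea, vomiting", and continues with muscle and joint pain, fatigue, chills and fever.

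Reactions off the list have two other routes. Unsolicited events are "All local and systemic AEs occurring 28 days following boost observed by the Investigator or reported by the participant". Medically attended events are asked about at study visits for up to 3 months after the boost.

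**The concern.** The solicited list is the measuring instrument for objective 4. A reaction on it is asked of everyone in the same way. A reaction off it is recorded only if the participant volunteers it, the investigator notices it, or the participant seeks care. Reports obtained by these two routes cannot be pooled or set side by side as if they were one measurement.

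The protocol expects both omitted reactions in more than one in ten recipients. At stake is whether the trial can say anything on solicited data about how often each occurs after this boost, and whether that differs by priming vaccine. The protocol itself fixes the list, and a symptom that was never asked about cannot be recovered at analysis, so a later statistical analysis plan cannot repair the omission.

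**Working it through.** The protocol gives no figure to reproduce here. The check sets two lists side by side and adds one piece of arithmetic for scale.

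**Step 1: item comparison.** The very common class in section 6.4 is split into single reactions and each is looked up under Solicited AEs.

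| Very common in section 6.4 | On the solicited lists? |
|---|---|
| Injection-site pain | Yes (local) |
| Injection-site swelling | Yes (local, no site stated) |
| Axillary lymphadenopathy | **No** |
| Headache | Yes |
| Nausea | Yes |
| Vomiting | **No** |
| Muscle pain | Yes |
| Joint pain | Yes |
| Fatigue | Yes |
| Chills | Yes |
| Fever | Yes |

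Result: 11 very common reactions, 9 solicited, 11 − 9 = 2 not solicited.

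**Step 2: the reverse comparison.** The solicited lists hold 4 local + 7 systemic = 11 items. Nine are those matched above. The other two are redness, which section 6.4 puts in the 1-10% class, and warmth, which section 6.4 does not mention. A frequency cut-off therefore does not explain the selection, and the protocol gives no other reason.

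**Step 3: neighbouring items.** Section 6.4 lists nausea and vomiting separately, and injection-site swelling and axillary lymphadenopathy separately. Nausea overlaps in part with vomiting. Swelling does not measure an armpit gland. Because the local item states no site, some participants could tick it for a gland and others not; whether the form words it more precisely cannot be seen from the protocol.

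**Step 4: scale.** Inputs: 400 participants, 200 per priming cohort (sections 3 and 4.4); about 10% loss to follow-up (section 4.4); a frequency above 10% (section 6.4). Expected number above n × 0.10:

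- per priming group: 200 × 0.10 = 20
- per priming group after loss: 200 × 0.90 × 0.10 = 18
- overall: 400 × 0.10 = 40, or 400 × 0.90 × 0.10 = 36 after loss

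This assumes that the frequency class carries over to this booster. Section 6.4 pools the Moderna and Pfizer vaccines and gives no booster rate, and sections 5, 5.1 and 6 leave the vaccine still to be chosen. The counts show order of magnitude only.

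**The case against.** The strongest reply is that a risk summary and a diary list serve different purposes. Nothing in the protocol requires one to mirror the other, so the choice of items is a preference and not a contradiction. That is fair as far as it goes. But the protocol offers no rationale, and a list that prompts for a less frequent and an unlisted reaction while leaving out two from the top class serves objective 4 less well than it easily could.

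Second, the outcome is worded as adverse events in the first 7 days, not solicited events only, and the 28-day unsolicited window contains those 7 days. This stands against reading the two reactions as wholly uncollected; capture is partial. It does not make unprompted reports comparable with prompted ones.

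A reader might go further and infer from section 9.2.1 ("Therefore, Aes will not be reported") that unsolicited events are lost altogether. The document does not support this. The same section first says that spontaneously reported and observed events will be recorded, and read literally its last sentence would remove the solicited events too. That inconsistency is a separate matter.

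A reader might also infer that total reactogenicity is understated. No total or composite score is defined, so there is no such quantity to understate. Both priming groups receive the same list, so the omission does not bias comparisons on the listed symptoms.

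Third, it can be said that adding the items would reveal little. With 200 per group and the 0.01 threshold of section 10, and assuming rates of 10% and 15% for illustration, the standard error is √(0.10 × 0.90/200 + 0.15 × 0.85/200) = 0.033. Then z = 0.05/0.033 ≈ 1.52 against a critical value of 2.576, which gives power of about 14%. This stands: a modest group difference would probably go undetected even if solicited, so the claim that the omission hides a difference is speculative. The gain is comparable description of both reactions, with some chance of seeing a large difference.

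**Conclusion.** The point holds in a limited form. Of the 11 reactions that section 6.4 calls very common, exactly two, axillary lymphadenopathy and vomiting, are not solicited. They cannot be compared between priming groups on solicited data for secondary objective 4. Lymphadenopathy is the main gap, because no listed item measures it; vomiting is the smaller one.

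The item count rests on the protocol's text alone. The figure of more than about 20 per priming group (18 after loss) rests on the assumption that the pooled >10% class applies to a booster not yet chosen. It should not be read as a forecast or as a lower bound for this trial.

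The effect is confined to one secondary objective. The primary endpoint and the sample size are untouched. The change is worth making because it is cheap and because the 7-day data cannot be collected afterwards.

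**What to change.** Before the first boost, amend the lists under Solicited AEs, and the diary and day 8 questionnaire with them:

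- add *swollen or tender glands in the armpit on the injected side*;
- add *vomiting*;
- word the local item as *swelling at the injection site*, so that it is not ticked for an armpit gland.

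If the two reactions were left out on purpose, a sentence giving the reason and reconciling the list with section 6.4 would at least make the choice visible, though it would not supply the data.

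The cost is two more items and one wording change on the diary and questionnaire, and two more comparisons in a secondary analysis. No visit, sample or treatment rule changes.

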### Unsolicited AEs

All local and systemic AEs occurring 28 days following boost observed by the Investigator or reported by the participant.

### Medically attended AEs

A medically attended AE, is defined as any adverse event for which the participant seeks medical attention either at hospital or from primary care. This explicitly excludes seeking medical attention solely for a SARS-CoV-2 test. Participants will be asked to record any medically attended AEs, either directly to the investigator or by filling in a questionnaire (every Study Visit). Medically attended AEs occurring up to 3 months post boost, will be directly solicited and reviewed at each study visit.

## 9.3 Annual safety report

In addition to the expedited reporting of SUSARs, the sponsor will submit, once a year throughout the clinical trial, a safety report to the accredited METC, competent authority, and competent authorities of the concerned Member States.

This safety report consists of:

- a list of all suspected (unexpected or expected) serious adverse reactions, along with an aggregated summary table of all reported serious adverse reactions, ordered by organ system, per study;
- a report concerning the safety of the subjects, consisting of a complete safety analysis and an evaluation of the balance between the efficacy and the harmfulness of the medicine under investigation.

## 9.4 Follow-up of adverse events

All SAEs will be followed until they have abated, or until a stable situation has been reached. Depending on the event, follow up may require additional tests or medical procedures as indicated, and/or referral to the general physician or a medical specialist. SAEs need to be reported till end of study within the Netherlands, as defined in the protocol.

## 9.5 [Data Safety Monitoring Board (DSMB) / Safety Committee]

If the subjects had not participated in this trial, they probably could have received the same vaccine via the national vaccination campaign at the end of this year with no

additional safety surveillance. Weekly investigator meetings will be held to discuss, among others, the different types of Aes.

## 10. STATISTICAL ANALYSIS

The data will be analysed as follows. *First*, the baseline characteristics of the sample will be described using descriptive statistics. Continuous variables will be presented as mean  $\pm$  standard deviation in case of a normal distribution or median (interquartile range) in case of non-normal distribution. Normality of the distribution of the continuous variable will be assessed by the Shapiro-Wilk test. Categorical variables will be presented as numbers (percentage). Differences in comparing two groups or arms for continuous variables will be compared using t-test or Mann-Whitney U-test (whichever appropriate based on the normality of the variable distribution). Pearson Chi-square test or Fisher's exact test will be used to examine differences for categorical variables (depending on minimum number of 5 observations per cell, respectively). For the primary outcome, measuring the fold change (day of boost and day 28) in the antibody response after an additional boost comparing Janssen and mRNA primed HCW. The difference between the Janssen and mRNA group will be assessed using a Mann Whitney U test. For the secondary outcomes, we will use similar statistical tests as described under the baseline characteristics. The analysis will be on an intention-to-treat basis. Taking into account a possible multiple-testing problem, we will use a p-value below 0.01 as a cut off to conclude statistical significance.

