### 4.4 Sample size calculation

The primary analysis of this study will consist of one comparison:

- The fold change (day of boost and day 28) in antibody response after an additional boost comparing Janssen and mRNA primed HCW in the direct boost arm.

The sample size calculation is based on the following assumptions:

- The sample size calculation takes the available data from the Erasmus MC HCW study.
- The log10 transformed difference in fold change 28 days after third vaccination (i.e., second booster after Janssen prime and first boost after mRNA prime) are *Janssen prime 1.344 (sd=0.451)*; *mRNA prime 1.151 (sd=0.449)*.
- The expected difference is estimated using the non-parametric Mann-Whitney U test (mean and standard deviations are used to estimated median and interquartile ranges). This procedure is readily available in G\*Power (version 3.1.9.7).

Based on the above assumptions, the study needs to recruit 91 patients in each arm to achieve 80% power at two-sided 5% significance level. We assume +/- 10% of study participants will be loss to follow-up. Therefore, the sample size in each arm will be 100 participants. The study contains two treatment arms and two groups resulting in a total sample size of 400 participants.

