### 11.2 Recruitment and consent

First, we will approach all people from the SWITCH and HCW study. If insufficient participants emerge from these studies, we will expand our search for healthcare workers in hospitals.

- Participants from SWITCH and HCW study will be approached by e-mail.

The group of persons that will be approached for this study are all Health Care Workers vaccinated once with Janssen or twice with Moderna or Pfizer and received at least one booster. Currently available vaccines have retained some degree of efficacy against all epidemiologically important SARS-CoV-2 variants that have emerged to date, with higher efficacy against hospitalization and death than against mild disease (6-11).

Results from observational studies have shown decreased effectiveness against certain variants (e.g. Omicron) and waning effectiveness over time. It is believed that revaccination will re-activate the immune memory leading to an improved protection against SARS-CoV-2.

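### The primary comparison is sized at two-sided 5%, but section 10 sets p<0.01 for significance without exempting it; if 0.01 governs that test, power is about 58%, not 80%

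*Protocol*

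**What the plan says.** Protocol section 4.4 (Sample size calculation) states that "The primary analysis of this study will consist of one comparison": the fold change from day of boost to day 28, Janssen-primed against mRNA-primed, in the direct boost arm. The planning values are mean log10 fold changes of 1.344 (SD 0.451) for Janssen and 1.151 (SD 0.449) for mRNA, with the Mann-Whitney U test. From these it concludes that "the study needs to recruit 91 patients in each arm to achieve 80% power at two-sided 5% significance level", and it raises the number to 100 per arm for about 10% loss to follow-up.

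Protocol section 10 (Statistical analysis) sets out, in one paragraph, the baseline description, the primary outcome with its Mann-Whitney U test, the secondary outcomes and the intention-to-treat basis. It ends: "Taking into account a possible multiple-testing problem, we will use a p-value below 0.01 as a cut off to conclude statistical significance". The sentence is not limited to secondary outcomes, and sections 10.1 to 10.4 say nothing further about significance levels.

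**The concern.** One test carries two significance levels in the same document. Section 4.4 supports its claim of 80% power with 5%. Section 10, taken as it reads, declares significance only below 1%. A sample size fixed for one level does not deliver the stated power at a stricter one.

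The conflict bears on the only comparison that was sized. If the p-value falls between 0.01 and 0.05, section 4.4 supports calling the difference significant and section 10 does not. Settling that once the result is known would be a choice of alpha made after seeing the data.

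**Working it through.** **Inputs, all from Protocol section 4.4 except the last**
- Means 1.344 and 1.151 log10; SDs 0.451 and 0.449
- Mann-Whitney U test, two-sided 5%, 80% power, 91 evaluable per arm
- 100 recruited per arm with about 10% loss, so about 90 evaluable
- Cut-off of 0.01 from section 10. Its sidedness is not stated; two-sided is assumed, as in the sizing.

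**Standardised effect**
- Difference: 1.344 − 1.151 = 0.193 log10, a ratio of 10^0.193 = 1.56
- Pooled SD: √[(0.451² + 0.449²)/2] = 0.450
- d = 0.193/0.450 = 0.429

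**Method.** Two-sample noncentral t, with n multiplied by 3/π, the efficiency of the Mann-Whitney test relative to the t-test for normal data. With n′ = n × 3/π, the noncentrality is d√(n′/2) and the degrees of freedom are 2n′ − 2.

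**Reproducing the plan at 5%.** For n = 91, n′ = 86.9, the noncentrality is 0.429 × √43.45 = 2.83, and the critical t is 1.974. Power is 80.3%, and 91 is the smallest n that reaches 80%, so the sponsor's figure is confirmed. A plain t calculation gives 87 and a plain normal approximation gives 86; neither matches.

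**Changing only the significance level**

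| Evaluable per arm | Power at two-sided 5% | Power at two-sided 1% |
|---|---|---|
| 90 | 79.8% | 58.2% |
| 91 | 80.3% | 58.9% |
| 100 (no loss) | 83.9% | 64.1% |

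At n = 91 the noncentrality stays at 2.83 while the critical t rises from 1.974 to 2.605.

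**Cross-checks.** Simulating the Mann-Whitney test on normal data (20,000 runs) gives 79.5% and 58.0% at n = 90, 80.4% and 58.4% at n = 91, and 83.8% and 64.1% at n = 100, at 5% and 1% respectively. Moving an exact 80% design from z = 1.960 to z = 2.576 gives Φ(1.960 + 0.842 − 2.576) = 58.9%.

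**What 80% power at 1% would take**
- At the planned difference: 135 evaluable per arm, or 135/0.90 = 150 recruited
- With 90 evaluable per arm: a true difference of 0.237 log10, a ratio of 10^0.237 = 1.73

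**How often the conflict would matter.** If the planning values are true, the p-value falls between 0.01 and 0.05 in about 79.8 − 58.2 = 21.6% of such trials with 90 evaluable per arm.

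**The case against.** The strongest reply is that 0.01 was meant for the other tests only. The sentence gives multiple testing as its reason and follows the line on secondary outcomes, while section 4.4 names a single primary comparison at 5%. That intent is plausible, and under it the 80% stands. But the sentence also follows the intention-to-treat statement, which covers every analysis, and it carries no restriction. The objection makes the 58% conditional; it does not remove the contradiction. For the same reason a reader should not infer that the trial simply has 58% power.

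A second reply is that the primary family does contain multiplicity. Section 10.1 lists two questions, level as well as fold change, antibodies as well as T-cell responses, and a possible Omicron BA.1 IgG test. Section 10.2 speaks of primary endpoints in the plural. This stands as far as it goes: a reader might infer from section 4.4 that there is nothing to correct for, and section 10.1 does not support so flat a statement. But if the sponsor relies on this argument, 0.01 does apply to the comparison in section 4.4 and its stated power is wrong.

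A third point limits the reach of the problem. The loss of power concerns the Janssen-versus-mRNA contrast. Whether antibodies rise at all after the boost is a different question: the planning means correspond to roughly 22-fold and 14-fold rises, which would be detected at either level. Nor does the protocol say that a non-significant contrast will be read as showing no difference by priming.

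A reader might also infer that the mRNA planning value is an error, because section 4.4 takes it from the "second booster after Janssen prime and first boost after mRNA prime" while section 11.2 approaches people who were "vaccinated once with Janssen or twice with Moderna or Pfizer and received at least one booster". The documents do not support that. Section 4.4 discloses the source of its figures openly, and the criteria in sections 4.2 and 4.3 do not require an earlier booster; that condition appears only in the description of whom to approach (sections 11.2 and 13.2). It is a stated assumption, separate from the conflict between the two levels.

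**Conclusion.** The point holds as an internal contradiction. The arithmetic in section 4.4 is correct at its own level; what fails is its agreement with the decision rule in section 10. If 0.01 governs the primary test, as the text reads, power for the planned difference is about 58–59% at the planned evaluable number and 64% with no loss, against the stated 80%. The chance of missing a difference of that size rises from about 2 in 10 to about 4 in 10. If 0.01 was meant only for the other tests, 80% stands and the defect is one of wording.

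The figures rest on the protocol's own means and SDs, on normally distributed log10 fold changes, and on a two-sided 0.01. An unseen statistical analysis plan would not remove the conflict, because the protocol itself fixes both levels.

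**What to change.** Before the data are analysed, adopt one of two resolutions:

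1. State in section 10 that the primary comparison named in section 4.4 is tested at two-sided 5%, and that 0.01 applies to all other tests. These should expressly include question 2, the T-cell outcomes and any BA.1 outcome listed in section 10.1, so that none is left without a level. Section 4.4 then stands unchanged.
2. Keep 0.01 for the primary comparison, say that it is two-sided, and restate its power in section 4.4 as about 58%.

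The first costs a sentence in section 10; the second costs a clause there and one figure in section 4.4. Neither adds participants. Keeping both 0.01 and 80% power would not be free: it needs about 135 evaluable, or 150 recruited, per arm in the comparison.

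A short table of power over a range of true differences would be useful alongside either choice, but it is optional.
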